**Methods:**

This is a single-centric, parallel-group, randomized controlled trial with blinded participants, outcome assessor, and statistician. One hundred twelve participants will be randomly assigned into the EA group or sham acupuncture (SA) group in a 1:1 ratio. The study will last for 22 weeks for each participant, including a 2-week baseline assessment period, an 8-week treatment period, and a follow-up for 12 weeks. The primary outcome is the change of mean weekly complete spontaneous bowel movements (CSBMs) during weeks 1 to 8 from baseline. Secondary outcomes include the change from baseline of mean weekly CSBMs during the follow-up period, mean weekly spontaneous bowel movements (SBMs), overall CSBM response rate, scores on Bristol Stool Form Scale (BSFS), straining level, Patient Assessment of Constipation Symptoms (PAC-SYM), Patient Assessment of Constipation Quality of life questionnaire (PAC-QOL), and Brief Psychiatric Rating Scale (BPRS). Adverse events and medicine use will be recorded as well.

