#### Exclusion criteria

Exclusion criteria include that (1) constipation caused by other reasons than antipsychotic drugs; (2) mental instability within baseline assessment period judged by clinicians; (3) severe heart, liver, kidney diseases, or any other considerable dysfunctions (e.g., gastrointestinal obstruction); (4) use of anticholinergic drugs or drugs for constipation (except for rescue medicine) within 2 weeks before randomization; (5) pregnant or breastfeeding women; (6) participants with a pacemaker, metal allergy, or severe fear of needling; (7) a history of acupuncture treatment within the past 3 months; and (8) participation in any other clinical trials meanwhile.

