### Interventions

Twenty sessions of 30-min treatment (3 sessions per week during the first 4 weeks and 2 sessions per week during the last 4 weeks) will be provided for all participants over 8 weeks. Acupoints for antipsychotic-related constipation were predefined by acupuncture experts according to the TCM theory. Licensed acupuncturists with experience of at least 3 years will offer the treatments required. Besides, all enrolled participants will receive a basic treatment of schizophrenia according to the Guideline for Prevention and Treatment of Schizophrenia, the second edition developed by the Psychiatric Branch of the Chinese Medical Association [20]. Diet and lifestyle will be similar among participants and medicine use will be supervised by nurses. Participants may discontinue their intervention if they have considerable conditions such as worsening constipation or mental instability, judged by assessors or clinicians. Participants with no bowel movements for at least 3 consecutive days will be allowed to use 5–10 mg enteric-coated bisacodyl or 110-ml glycerol as rescue medicines. Additional treatment for constipation will be avoided as possible during this study.

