### Outcomes

#### Primary outcome

The primary outcome is defined as the change of mean weekly CSBMs over the 8-week treatment period from baseline, which will be obtained from a stool diary (calculating formula shown in Fig. 2). The stool diary is regarded as a valid instrument to reflect bowel habits in constipated participants [24]. The caregivers for participants will be trained to complete stool diaries during the whole period of the study. Weekly defecation frequency, stool consistency (types 1–7 on BSFS), straining level (scores from 0 to 4 representing the difficulty of defecation increasingly), a complete sense of each bowel movement (yes or no), medicine use, or other assistant methods will be recorded. The Schedule of each outcome assessment is illustrated in Fig. 3.

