##### Use of rescue medicine and other assistant methods

The use of rescue medicine and other assistant methods will be documented in stool diaries. The proportion and frequency of participants using rescue medicine or other assistant methods will be reported and compared between groups.

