### Statistical analysis

A professional statistician who is blinded to the allocation will analyze data using IBM SPSS21.0. Continuous variables will be presented as mean (standard deviation) or the median (interquartile range) based on data distribution. Categorical variables will be described by frequencies and percentages. Statistical analysis will follow the intention-to-treat principle predominately for participants who have been randomized. Missing data for the primary outcome will be imputed using the multiple imputation method. The alternative hypothesis is that there is a significant difference between EA and SA groups in the change of mean weekly CSBMs over an 8-week treatment period from baseline.

For the primary outcome, analysis of covariance (ANCOVA) model will be used with treatment and corresponding baseline value as covariates. Repeated measures ANCOVA with the same covariates will be implemented for change from the baseline of mean weekly CSBMs during the follow-up period, and change from baseline of mean weekly SBMs. An independent *t* test or Wilcoxon rank-sum test will be implemented for scores on BSFS, straining level, BPRS, credibility and expectancy, and mean weekly frequency of rescue medicine and other assistant methods used. The difference in overall CSBM response rate, blinding, adverse events, and proportion of participants using rescue medicine or other assistant methods will be compared using the Pearson *χ*^2^ test or Fisher’s exact test. Repeated measures ANOVA or Kruskal-Wallis *H* test will be implemented for scores on PAC-SYM and PAC-QOL. All significance levels will be set at 0.05 (two-sided) with confidence intervals reported.

As sensitive analyses, a per-protocol analysis will exclude data from participants who complete less than 16 sessions (80% of total treatment sessions) or use other medicines to treat constipation for more than 3 days per week on average. No additional analyses will be performed.

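### Rescue frequency is compared without the baseline rescue use already in the diary; adjusting for it is a free, modest gain, and the any-use proportion should be read as supportive only

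*Protocol article*

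**What the plan says.** Under Use of rescue medicine and other assistant methods: "The proportion and frequency of participants using rescue medicine or other assistant methods will be reported and compared between groups". Statistical analysis assigns the tests. The t test or Wilcoxon rank-sum test covers "mean weekly frequency of rescue medicine and other assistant methods used", and the "proportion of participants using rescue medicine or other assistant methods will be compared using the Pearson" chi-square test or Fisher's exact test. Neither has a baseline term, and the section ends by ruling out further analyses.

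The same section treats other diary outcomes differently. For the primary CSBM outcome an "analysis of covariance (ANCOVA) model will be used with treatment and corresponding baseline value as covariates", and repeated measures ANCOVA with the same covariates is used for follow-up CSBMs and for SBMs.

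Three other places bear on this:
- Interventions: "Participants with no bowel movements for at least 3 consecutive days will be allowed to use" rescue medicine.
- Exclusion criteria: the drug exclusion covers "drugs for constipation (except for rescue medicine) within 2 weeks before randomization", so rescue use is compatible with entry.
- Primary outcome: "The caregivers for participants will be trained to complete stool diaries during the whole period of the study". Medicine use and other assistance are among the diary items. The abstract describes the study as "including a 2-week baseline assessment period, an 8-week treatment period, and a follow-up for 12 weeks".

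**The concern.** A baseline measure of the outcome is collected, is likely to correlate with the outcome, and is left out of the comparison. Leaving it out widens the confidence interval and saves nothing. Under the Diagnose criteria section, a movement counts as spontaneous only if nothing assisted it in the previous 24 hours. Rescue use therefore affects which movements enter the CSBM count, and readers will look to the rescue comparison when they interpret the primary result.

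The proportion raises a second, conditional issue. Participants enter with fewer than 3 SBMs per week and may use rescue after 3 days without a movement. If most who become eligible take it, nearly everyone in both arms is a user, and a non-significant chi-square test could be taken for balance in rescue use.

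**Working it through.** **Plan's own figure.** Inputs from Sample size: difference 1.8 − 0.9 = 0.9, SD 1.6, two-sided 0.05, power 0.80. n = 2(1.960 + 0.842)² × 1.6² / 0.9² = 49.6, so 50 per group; 50/0.90 = 55.6, so 56; total 112. This reproduces. It concerns the primary outcome; the article gives no rescue rate and no power for rescue.

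**Is baseline rescue use available?** Rescue is exempt from the pre-randomization drug exclusion, the diary runs through the whole study, and it records medicine use and assistance. The baseline CSBM value comes from the same diary. So the covariate exists.

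**Who becomes eligible for rescue?** With k bowel-movement days in 56, there are k + 1 gaps. Keeping each to at most 2 days needs 56 − k ≤ 2(k + 1), so k ≥ 18, or 18/8 = 2.25 per week, almost evenly spaced. Anyone below that must meet the trigger, and most people somewhat above it will by chance.

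**Eligibility is not use.** Daily-movement simulation (assumed mean 2 to 3.9 movements per week, between-person CV 0.4, the same uptake for everyone), share with any use over 8 weeks:
- every trigger used: 98–100%
- 50% uptake: 91–99%
- 25% uptake: 75–92%
- 10% uptake: 44–65%

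**Effect of adjustment by formula.** With baseline–outcome correlation ρ, ANCOVA multiplies the residual SD by √(1 − ρ²). Unadjusted power of 0.80 becomes 0.84 at ρ = 0.3, 0.90 at 0.5 and 0.94 at 0.6.

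**Power at 50 per group, daily model.** Assumed: 2 movements per week at baseline, rising by 0.9 (SA) and 1.8 (EA). These rises are the CSBM figures from Sample size, borrowed for want of others. 800 replicates.

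| Uptake per trigger | Any use SA / EA | Any-use test | t | Wilcoxon | ANCOVA | ρ |
|---|---|---|---|---|---|---|
| 100% | 100% / 100% | 0.00 | 0.968 | 0.964 | 0.988 | 0.35 |
| 50%, uniform | 98% / 94% | 0.026 | 0.785 | 0.752 | 0.792 | 0.13 |
| 50%, varying by person | 87% / 83% | 0.095 | 0.424 | 0.348 | 0.556 | 0.57 |
| 25%, varying | 61% / 55% | 0.108 | 0.206 | 0.141 | 0.295 | 0.61 |
| 10%, varying | 30% / 26% | 0.079 | 0.101 | 0.076 | 0.134 | 0.61 |

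Gain of ANCOVA over the t test: about 2, 1, 13, 9 and 3 points. The simulation standard error is up to about 1.8 points (√(0.25/800)), so the smallest gains are close to nil.

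**Power under a second model.** Gamma-distributed gaps (shape 1.5 to 6), 2.7 vs 3.6 or 3.6 vs 4.5 movements per week, 10–100% chance of rescue per eligible day, 50 per group:
- Rescue taken whenever allowed: any use 60–99% (EA) vs 82–100% (SA). Power 0–64% for any use, 79–98% for unadjusted frequency, 83–100% for adjusted frequency.
- 30% uptake: 10–49%, 34–71% (t test) and 45–88%.
- Whole grid: adjustment added about 2 to 19 points over the t test.

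**The case against.** The strongest reply is that nothing here is wrong. Under randomization an unadjusted t or Wilcoxon test is valid. Frequency is compared alongside the proportion and does not saturate. Where the ceiling on any use is real, the planned frequency test already performs well: 0.96–0.97 in the daily model and 79–98% in the gap model. Where its power is poor, uptake is low or uneven and the proportion is well short of 100%. A two-week count is also a noisy covariate, and at 10% uptake adjustment only moves power from 0.10 to 0.13. This is a supporting secondary outcome, and every rescue figure rests on assumptions.

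Most of that stands, and it rules out a stronger reading. A reader might infer that the 3-day trigger drives any use to nearly 100% in both arms, so that a real difference in rescue use is easily missed. The documents do not support this. Rescue is allowed, not required, and no uptake is stated. The entry criterion counts spontaneous movements, whereas the trigger counts any movement. The ceiling and the weak frequency test also arise under different conditions. Nor do the documents show that the proportion test must go or that a negative binomial model is needed; the latter was not simulated, and both are matters of preference.

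What survives is narrower. The plan fixes an unadjusted test and closes its list of analyses, although the covariate is already collected and baseline adjustment is its own practice for CSBMs and SBMs.

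**Conclusion.** A free improvement on a secondary outcome, not an error. Omitting baseline rescue frequency costs roughly 1 to 19 points of power against the t test. The gain is near zero when uptake is uniform at about half of triggers, and in the daily model it is largest when uptake differs between participants. The range depends on assumed movement rates, spacing, uptake and a borrowed treatment effect; the article states none of these for rescue.

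The any-use proportion is likely to be uninformative only if uptake is moderate to high. Its test had power of 0.11 or less in the daily-model runs tabulated, but up to 64% in the gap model, so it is usually the weaker comparison rather than a worthless one. The primary analysis and the 50/56/112 sample size are untouched.

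**What to change.** In Statistical analysis, take rescue frequency out of the t test/Wilcoxon list and state:
- Mean weekly frequency of rescue or other assistance over weeks 1 to 8 is analysed by ANCOVA with treatment and baseline-period weekly frequency as covariates, and the adjusted difference is reported with its 95% CI. A count model with the same covariates is an acceptable alternative.
- This is the main rescue comparison. The any-use proportion, over the same weeks, is supportive, and a non-significant result from it is not to be read as equal rescue use.

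The cost is a few sentences. No new data, visits or participants are needed and the rescue rule is unchanged. Trial status reports that recruitment has not begun, so the change can be made before any data exist.

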### Randomization

According to the allocation schedule, participants will be randomly assigned into the EA group or SA group in a 1:1 ratio. An independent statistician unrelated to the final statistical analysis will generate a randomization sequence using SPSS Statistics, version 21.0 (International Business Machines Corporation, China). Numbered opaque envelopes that containing allocation codes will remain sealed until the first treatment. An independent researcher is available to open the corresponding envelope and complete the allocation. The assigned result will be informed to the acupuncturist only.

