##### Patient Assessment of Constipation Symptoms (PAC-SYM)

The PAC-SYM is commonly used to value the presence and severity of constipation on 3 subscales including abdominal symptoms, stool symptoms, and rectal symptoms [26]. A scoring range of 0 to 4 is derived for each item. The PAC-SYM will be measured at baseline, week 4, and week 8.

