##### Patient Assessment of Constipation Quality of life questionnaire (PAC-QOL)

PAC-QOL is capable to reflect life quality related to constipation on four subscales by scoring 28 items including physical discomfort, psychosocial discomfort, worries and concerns, and satisfaction [27]. In each item, the score ranges from 0 to 4 with lower scores indicating greater impairment or dissatisfaction. PAC-QOL will be assessed at baseline, week 4, and week 8.

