### Sample size

Referring to a previous study [30], the change from baseline in mean weekly CSBMs during week 1 to week 8 is about 1.8 in the EA group and 0.9 in the SA group with a standard deviation of 1.6. A calculated sample size of 50 participants in each group is estimated based on a significant level of 0.05 and a statistical power of 0.8. When considering a dropout rate of 10%, 56 participants are needed in each group, 112 participants in total.

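### PAC-SYM and PAC-QOL are to be analysed without the baseline covariate used for the bowel-movement outcomes, and the named non-parametric alternative is not a repeated measures method

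*Protocol article*

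**What the plan says.** The Secondary outcomes section of the protocol article sets the same three visits for both scales: "The PAC-SYM will be measured at baseline, week 4, and week 8" and "PAC-QOL will be assessed at baseline, week 4, and week 8". That is one pre-treatment and two on-treatment assessments.

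The Statistical analysis section then fixes the test: "Repeated measures ANOVA or Kruskal-Wallis *H* test will be implemented for scores on PAC-SYM and PAC-QOL". It names no covariate. It does not say whether baseline is a level of the time factor, and it does not say whether the group term or the group-by-time term is the test of treatment.

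The same section handles other outcomes differently. For the primary outcome, an "analysis of covariance (ANCOVA) model will be used with treatment and corresponding baseline value as covariates". For later CSBM periods, "Repeated measures ANCOVA with the same covariates will be implemented for change from the baseline of mean weekly CSBMs during the follow-up period", and the sentence extends this to SBMs. There are two arms: "participants will be randomly assigned into the EA group or SA group in a 1:1 ratio". On error level and reporting: "All significance levels will be set at 0.05 (two-sided) with confidence intervals reported".

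**The concern.** There are two separate problems.

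**The fallback is the wrong kind of test.** Kruskal-Wallis compares independent groups. With two arms it reduces to the Wilcoxon rank-sum test, so it can compare the arms at one visit or on one summary score. Applied to a raw score it uses neither the repeated visits nor the baseline. The article does not say which visit or summary it would be applied to.

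**The baseline score is collected but not used as a covariate.** If baseline is a level of time, the group main effect averages in a visit at which treatment cannot yet have acted, and the group-by-time term is a two-degree-of-freedom omnibus test. If only weeks 4 and 8 are modelled, the precision that baseline offers is left unused.

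At stake is the chance of detecting a real effect on symptoms and constipation-related quality of life. Leaving the tested term open also matters, because the candidates differ widely in power.

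**Working it through.** **1. The plan's own figure.** The Sample size section assumes that the mean change "is about 1.8 in the EA group and 0.9 in the SA group with a standard deviation of 1.6". The difference is 1.8 − 0.9 = 0.9, and the standardised effect is 0.9 / 1.6 = 0.5625. With two-sided alpha 0.05 and power 0.80, n per arm = 2 × (1.96 + 0.842)² × 1.6² / 0.9² ≈ 49.6, so 50. Allowing for 10% dropout, 50 / 0.9 = 55.6, so 56 per arm and 112 in total. The figure reproduces, but it concerns the primary outcome only. The article gives no effect size, SD or correlation for PAC-SYM or PAC-QOL.

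**2. Assumptions for the comparison.** These are not from the article, except that 50 per arm is its evaluable number:
- n = 50 per arm
- effect d = 0.5 SD at both week 4 and week 8
- compound symmetry with correlation r = 0.3, 0.5 or 0.7 between any two visits
- two-sided alpha 0.05

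Power comes from the noncentral F distribution with λ = (n/2) × I = 25 × I.

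**3. Information I for each reading, with the numbers at r = 0.5**
- Group main effect, baseline as a level: I = (2d/3)² / ((1 + 2r)/3) = 0.1111 / 0.6667 = 0.167; λ = 4.17 on 1 df.
- Group-by-time, baseline as a level: I = (2/3)d² / (1 − r) = 0.1667 / 0.5 = 0.333; λ = 8.33 on 2 df.
- Weeks 4 and 8 only, no baseline: I = d² / ((1 + r)/2) = 0.25 / 0.75 = 0.333; λ = 8.33 on 1 df.
- Kruskal-Wallis on the raw week-8 score: I = 0.955 d² = 0.239; λ = 5.97. The factor 0.955 is the efficiency of the rank-sum test relative to the t test under normality.
- Baseline-adjusted average of weeks 4 and 8: I = d² / ((1 + r)/2 − r²) = 0.25 / 0.5 = 0.500; λ = 12.5 on 1 df.
- Baseline-adjusted week 8 alone: I = d² / (1 − r²) = 0.25 / 0.75 = 0.333; λ = 8.33 on 1 df.

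**4. Power**

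| Analysis | r = 0.3 | r = 0.5 | r = 0.7 |
|---|---|---|---|
| Group main effect, baseline as a level | 62% | 52% | 45% |
| Group-by-time, baseline as a level | 57% | 73% | 92% |
| Weeks 4 and 8, no baseline | 87% | 82% | 77% |
| Kruskal-Wallis, raw week-8 score | 68% | 68% | 68% |
| Baseline-adjusted average of weeks 4 and 8 | 91% | 94% | 98% |
| Baseline-adjusted week 8 alone | 74% | 82% | 93% |

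**5. Sensitivity to the assumed effect.** With the primary outcome's 0.5625 borrowed as the effect, the adjusted average has power 96% / 98% / 99.6%. The group main effect has 72% / 62% / 55%, group-by-time 68% / 83% / 97%, weeks 4 and 8 without baseline 93% / 90% / 86%, and Kruskal-Wallis 78%. The adjusted average is again highest at every correlation.

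If the week-4 effect is half the week-8 effect (0.5625 at week 8), then as r goes from 0.3 to 0.7:
- the adjusted average has 80% to 94%
- the adjusted week-8 difference has 83% to 97%
- group-by-time has 55% to 91%
- the group main effect has 48% to 34%

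So with a delayed effect the week-8 contrast becomes slightly the stronger of the two adjusted ones.

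**6. Kruskal-Wallis against rank-sum.** On one simulated two-group sample of 50 per arm, both tests gave p = 0.0086 (rank-sum without continuity correction), as the algebra requires.

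**The case against.** A reader might infer that baseline is certainly in the repeated measures ANOVA and that most of the information is therefore lost. Three visits, an analysis of scores, and ANOVA rather than ANCOVA do point that way, and the adjusted average would then carry 2.1, 3.0 or 5.0 times the information of the group main effect at r = 0.3, 0.5 or 0.7. The article does not support this as a general statement. It never says that baseline is a time level, and a condensed article may leave factor levels and the tested term to the analysis plan. Those ratios belong to the least favourable term only. Against group-by-time, the usual test when baseline is a level, the ratio is 1.9, 1.5 or 1.25, though that term spreads its noncentrality over 2 df.

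The comparator also matters. The 94% at r = 0.5 is for the average of weeks 4 and 8. If week 8 alone is the reported contrast, the gain over group-by-time is 82% against 73% at r = 0.5, and only 93% against 92% at r = 0.7. Against weeks 4 and 8 without baseline, week 8 alone is lower at r = 0.3 (74% against 87%).

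Nor does the article show that no week-8 difference would be available: it promises confidence intervals and does not rule out visit-specific contrasts. Baseline adjustment is not its universal rule either, since BSFS, straining level and BPRS get t or rank-sum tests. In a randomised two-arm comparison, leaving out the baseline covariate costs efficiency and does not cause bias.

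These objections limit the size of the point but do not remove it. The Kruskal-Wallis fallback is misnamed on any reading. It could be applied to change scores and so use baseline, but it still would not handle repeated visits. The adjusted average also has the highest power in every column of the table.

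**Conclusion.** The point holds as one of efficiency and specification. The protocol fixes, for two scales with one baseline and two later visits, an analysis with no baseline covariate and a fallback that is not a repeated measures method. Its own text already contains the better approach for CSBMs and SBMs.

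The size depends on what was intended. Under the assumptions in the working (0.5 SD at both visits, compound symmetry, correlation 0.3 to 0.7), the adjusted average of weeks 4 and 8 gains about 4 to 21 percentage points over weeks 4 and 8 without baseline (91 − 87 and 98 − 77). It gains 34 down to 6 over group-by-time (91 − 57 and 98 − 92), and 29 to 53 over the group main effect with baseline as a level (91 − 62 and 98 − 45). None of the effect, SD or correlation values for these scales comes from the article.

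Both outcomes are secondary. The validity of the tests, the primary analysis and the sample size are unaffected. The change is worth making, and it is timely because the Trial status section reports that recruitment has not begun.

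**What to change.** Replace the sentence on PAC-SYM and PAC-QOL in the Statistical analysis section with the protocol's own approach:
- Analyse the week-4 and week-8 scores by repeated measures ANCOVA or a linear mixed model with treatment, visit, treatment-by-visit and the baseline score.
- Name the baseline-adjusted treatment difference averaged over weeks 4 and 8 as the main contrast, with its 95% CI, and report the week-8 adjusted difference alongside it.
- Delete Kruskal-Wallis. As the fallback for clearly non-normal scores, name a rank-based ANCOVA on baseline.

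The cost is one or two sentences of text. The visits, the data and the software (SPSS) stay the same, and no change to the sample size is needed.

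### The protocol's only sensitivity analysis cannot test the imputation behind the primary result, and its wording rules out one that could

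*Protocol article*

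**What the plan says.** Under Statistical analysis, the protocol article analyses the primary outcome (change from baseline in mean weekly CSBMs over weeks 1 to 8) by ANCOVA, mainly by intention to treat. On missing values it says: "Missing data for the primary outcome will be imputed using the multiple imputation method".

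One sensitivity analysis follows, a per-protocol analysis. It leaves out participants with fewer than 16 of the 20 sessions, and those who "use other medicines to treat constipation for more than 3 days per week on average". The section then closes: "No additional analyses will be performed".

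Four other sections bear on the point:
- Interventions: "Participants may discontinue their intervention if they have considerable conditions such as worsening constipation or mental instability".
- Sample size: a 10% dropout allowance takes 50 per group to 56.
- Data collecting method: people who stop the intervention are to be encouraged to go on with the diary and the other assessments. Caregivers keep the diary.
- Overall CSBM response rate: a participant who leaves the study early counts as a non-responder for the remaining weeks. This rule serves that secondary outcome only.

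**The concern.** Multiple imputation in its usual form assumes that, given what has been observed, missing diary weeks resemble the recorded weeks of comparable participants. The data cannot confirm this. The normal safeguard is to re-run the primary analysis under a stated departure from the assumption and see whether the conclusion survives.

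Here one route to missing data may run through the outcome itself, since worsening constipation is a ground for stopping treatment and some who stop may also stop providing diaries. If imputation credits them with the improvement seen in those who stayed, the treatment difference could be wrong, and no planned analysis of the primary outcome would show it.

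This is not a detail left to a statistical analysis plan. The article says what will be done and excludes the rest, so a later plan that added such a check would contradict it.

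**Working it through.** **1. The plan's own figure.** Inputs from Sample size: a change that "is about 1.8 in the EA group and 0.9 in the SA group with a standard deviation of 1.6", "based on a significant level of 0.05 and a statistical power of 0.8". Statistical analysis makes the test two-sided, and allocation is 1:1.
- n per group = 2 × (1.96 + 0.8416)² × 1.6² / 0.9² = 2 × 7.849 × 2.56 / 0.81 = 49.6, so 50.
- With 10% dropout: 50 / 0.90 = 55.6, so 56 per group and 112 in total.

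The sample size reproduces and is not in dispute.

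**2. What the per-protocol set removes.** The schedule gives 3 × 4 + 2 × 4 = 20 sessions, and 16/20 = 80%. A participant who attends every session reaches 12 + 2 × 2 = 16 at the end of week 6. Anyone who stops treatment before then is excluded. If they also stop the diary, they are the people with the most missing weeks. The analysis therefore discards the participants for whom the imputation matters most. Agreement with the primary result would not show that their imputed values were sound.

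**3. Illustrative size.** The documents give only the 10% dropout and the planning means. The rest is assumed: dropout at the very start, imputation at the arm mean, and a true change of zero in those missing.
- Overstatement = d_EA × 1.8 − d_SA × 0.9, where d is the proportion missing in each arm.
- 10% in both arms: 0.10 × 1.8 − 0.10 × 0.9 = 0.18 − 0.09 = 0.09.
- Check: the true arm means are 0.9 × 1.8 = 1.62 and 0.9 × 0.9 = 0.81, so the true difference is 0.81 against 0.90 as imputed. The excess is 10% of 0.9.

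**4. How it varies.**
- Later dropout: if those who leave matched their arm mean for 4 of the 8 weeks, only half the period is affected, giving 0.09 × 4/8 = 0.045.
- More dropout in sham, 5% EA and 10% SA: 0.09 − 0.09 = 0.
- 5% EA and 15% SA: 0.09 − 0.135 = −0.045, so the effect is understated.
- More dropout in EA raises the overstatement.
- Equal missingness with the same shift in both arms gives no bias. The 0.09 arises because a return to zero is a larger shift in EA (1.8) than in sham (0.9).

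**5. Against the precision of the trial.** With 50 per group, SE = 1.6 × √(2/50) = 0.32, and the smallest significant difference is about 1.96 × 0.32 = 0.63. An error of 0.09 is 0.09/0.32 = 0.28 SE. With 10% missing in EA and a shift in that arm only, an observed difference of 0.70 loses significance at a shift of (0.70 − 0.627)/0.10 ≈ 0.7 CSBMs per week. One of 0.90 needs (0.90 − 0.627)/0.10 ≈ 2.7. A result near the threshold is fragile; one at the planned effect is not. These figures ignore any precision gained from baseline adjustment or lost through imputation.

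**The case against.** The strongest reply is that stopping treatment is not the same as missing data. The Interventions sentence concerns the intervention, not the study. Diaries are kept by caregivers of participants recruited as inpatients, supervised by the outcome assessor, and are meant to continue after treatment stops. Someone who worsens and then leaves would often have diary weeks recording the worsening, and an imputation model can use them. All of this stands. It makes informative missingness a possibility and limits its likely size, but encouragement does not guarantee data, and the sponsor itself allows for 10% dropout.

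The non-responder rule already treats early leavers cautiously on the same diary variable. That also stands, but it applies to a secondary binary outcome and does not test the primary estimate.

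The closing sentence may have been aimed at subgroup or adjusted analyses. That is possible, but as written it covers everything, which is reason enough to reword it.

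A reader might infer more from the text than it supports:
- That the bias must favour EA, or is large. This needs dropout concentrated in EA, for which the documents give no figure. If EA works as planned and worsening drives dropout, excess dropout in sham is at least as plausible.
- That the per-protocol medication threshold is too generous to exclude anyone. No figure in the documents gives the use of other constipation medicines. The rescue rule does not supply one, since it concerns rescue use and does not cap repeat use when a rescue fails.

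**Conclusion.** The point holds in a limited form. The protocol commits the primary result to multiple imputation, offers as its only check an analysis that cannot examine the imputation assumption, and by its wording excludes one that could. The documents do not show that missingness will be informative, nor in which direction any bias would run.

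Under the assumptions in step 3 of the working, the overstatement is at most 0.09 on 0.9 (10%) when 10% are missing in both arms. It is smaller with later dropout and may be cancelled or reversed if sham loses more participants. This should be corrected because it is cheap and could matter for a borderline result. It does not undermine the design or the sample size.

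**What to change.** Narrow the closing sentence of Statistical analysis so that it no longer bars sensitivity analyses of the primary outcome; if it was meant for subgroup or adjusted analyses, it should say so.

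Prespecify one sensitivity analysis of the primary ANCOVA in all randomised participants. It should use delta-adjusted imputation, or reference-based imputation (to sham or to baseline), and apply it only to diary weeks that are actually missing. Weeks recorded after treatment has stopped stay as observed. Report a tipping-point delta that is allowed to differ by arm, so that departures in either direction are seen. The per-protocol analysis can remain as a separate question about adherence.

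The cost is a few extra model runs and a sensitivity estimate that may be less favourable than the primary one. The sample size stays at 112. Trial status reports that recruitment had not begun, so on that account the change can be made before any data exist.
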